## Abstract

**Background:**

Chemotherapy-induced peripheral neuropathy (CIPN) is the main dose-limiting side effect of neurotoxic chemotherapeutic agents. CIPN can lead not only to loss of physical function, difficulties in activities of daily living (ADLs), and decreased quality of life, but also to dose reduction, delay or even cessation of treatment. Currently, there are few proven effective treatments for CIPN. This randomized controlled clinical trial is designed to evaluate the effects and safety of electroacupuncture (EA) for patients with CIPN.

**Methods/design:**

This is a multicenter, two-armed, parallel-design, patient-assessor-blinded, randomized, sham-controlled clinical trial. Forty eligible patients with CIPN will be randomized in a ratio of 1:1 to the EA or sham EA arms. During the treatment phase, patients will undergo eight sessions of *verum* EA or sham EA twice weekly for four weeks, and then will be followed-up for eight weeks. Electrical stimulation in the EA group will consist of a mixed frequency of 2/120 Hz and 80% of bearable intensity. Sham EA will be applied to non-acupoints, with shallow needle insertion and no current. All outcomes and analyses of results will be assessed by researchers blinded to treatment allocation. The effects of EA on CIPN will be evaluated according to both subjective and objective outcome measures. The primary outcome measure will be the European Organization for Research and Treatment of Cancer (EORTC) quality of life questionnaire to assess CIPN (QLQ-CIPN20). The secondary outcome measures will be the results on the numerical rating scale, the Semmes-Weinstein monofilament test, the nerve conduction study, and the EORTC QLQ-C30, as well as the patient’s global impression of change and adverse events. Safety will be assessed at each visit.

**Discussion:**

The results of this on-going study will provide clinical evidence for the effects and safety of EA for CIPN compared with sham EA.

**Trial registration:**

Clinical Research Information Service: KCT0000506

## Background

Chemotherapy-induced peripheral neuropathy (CIPN) is defined as damage to the peripheral nervous system induced by neurotoxic chemotherapeutic agents, including platinum compounds such as oxaliplatin and cisplatin, taxanes such as paclitaxel and docetaxel, and vinca alkaloids like vincristine [1,2]. Although the symptoms of CIPN vary according to the type and severity of the motor, sensory, and autonomic nerves that are affected, most symptoms of CIPN are sensory and include numbness, tingling, and shooting and burning pains in the toes and fingers, progressing proximally in a typical ‘glove and stocking’ distribution. Furthermore, CIPN in most patients is only partially reversible and can persist long after treatment is terminated [3]. CIPN is one of the major dose-limiting side effects of chemotherapy and can lead not only to loss of physical function, difficulties in activities of daily living (ADLs), and decreased quality of life (QOL), but also to dose reduction or delay or even cessation of treatment [4,5].

Dose and treatment schedule modifications of neurotoxic chemotherapy are currently the primary methods used for the non-pharmacological management of CIPN [3]. Alternative dosing regimens and treatment modification schemes have been found to be effective in reducing the incidence and/or severity of CIPN [6,7]. These strategies, however, can potentially affect tumor response and disease progression. Several pharmacologic agents useful in treating peripheral neuropathy caused by other conditions such as diabetes, have been investigated as treatment for CIPN; these include anticonvulsants such as gabapentin and lamotrigine, and tricyclic antidepressants. To date, however, no agent has proven effective in the treatment or mitigation of CIPN [8,9], underscoring the need for the development of novel treatments.

Acupuncture is a popular and safe treatment intervention used to manage various conditions including peripheral neuropathy. Electroacupuncture (EA) has been found to be effective in treating diabetic peripheral neuropathy [10], neuropathic pain including post-herpetic neuralgia and post-traumatic neuropathy [11], and human immunodeficiency virus (HIV)-related peripheral neuropathy [12]. Clinical trials in patients with CIPN have shown that acupuncture/EA alleviated symptoms [13-17] and improved nerve conduction study (NCS) results [18], suggesting that EA may be an effective treatment for CIPN without causing adverse effects. Most prior studies, however, were case reports, case series, or clinical trials lacking a control group, resulting in a high risk of bias. A recent Cochrane Review on acupuncture for cancer pain included three randomized controlled trials (RCTs), only one of which was of high methodological quality [19]. In addition, few RCTs have evaluated EA for CIPN, underscoring the need for well-designed robust clinical trials to provide evidence for EA in treating CIPN.

### Aim of the study

The aim of this study is to test the feasibility of a RCT to investigate effectiveness and safety of EA, compared with sham EA, in the treatment of CIPN. We will evaluate whether EA improves symptoms and functioning, cutaneous sensation, nerve conduction, and QOL. All adverse events will also be assessed.

The results of this study will provide evidence for the feasibility of this clinical trial design and also yield data to determine the appropriate sample size for future large-scale RCTs of EA in cancer patients with neuropathy.

## Methods/design

### Study design and ethics

This is a patient-assessor-blinded, randomized, sham-controlled clinical trial with two parallel arms. The trial will be conducted at two clinical research centers in Korea; Kyung Hee University Hospital at Gangdong and Dongguk University Ilsan Oriental Hospital, in accordance with the Declaration of Helsinki and the Guidelines for Good Clinical Practice. This research protocol has been reviewed and approved by the institutional review boards (IRB) of each trial center (KHNMC-OH-IRB 2012-007 and 2012-01). Written informed consent will be obtained from all study participants prior to enrollment. Eligible participants will be randomized in a ratio of 1:1 to the EA or sham EA arm and receive treatment for four weeks. Patients will be followed-up for two months thereafter (Figure 1). Participants will be evaluated and results will be analyzed by professionals blinded to group allocation. This protocol has been registered with the ‘Clinical Research Information Service’ of the Republic of Korea, a registry in the WHO Registry Network.

**Figure 1 F1:**
[figure not shown]
Flowchart showing the steps in patient recruitment, treatment, and analysis.

### Participants

#### Inclusion criteria

Patients will be eligible if they are aged 18 years or older, have received or are currently receiving neurotoxic chemotherapy, have experienced symptoms of chemotherapy-induced peripheral neuropathy for ≥ one month, and have scores ≥ 4 on 10 on the numerical rating scale (NRS). Eligibility criteria will also include no use of medication to prevent or treat neuropathy for two weeks before screening or stability of medication to prevent or treat neuropathy for two months before screening; an Eastern Cooperative Oncology Group (ECOG) performance status (PS) of 0 to 2; life expectancy of ≥ six months; and provision of written informed consent.

Stable medication is defined as no change in the type and dose of medication to prevent or treat neuropathy for > two months before enrollment. Patients receiving any of those drugs will have to remain on the same medications and doses throughout the study period. Patients requiring a change in the type and dosage of medication will be withdrawn from the study.

#### Exclusion criteria

Exclusion criteria are pre-existing peripheral neuropathy or a history of peripheral neuropathy due to any cause other than chemotherapy (for example, diabetes, peripheral vascular disease, HIV, alcohol, toxins, hereditary factors and nerve compression injuries); known hypersensitivity to acupuncture or inability to cooperate with the acupuncture procedure; treatment with traditional Korean medical protocols, including acupuncture, moxibustion, cupping or herbal medicine, for peripheral neuropathy during one month before enrollment; cardiovascular disorder including arrhythmia or use of a pacemaker; pregnancy or potential pregnancy and nursing; and unwillingness to comply with this study protocol.

### Randomization and allocation concealment

A total of 40 participants who meet the eligibility criteria will be randomised in a ratio of 1:1 to the EA or sham EA group. In this trial, constant exposure to neurotoxic agents and concomitant use of neuropathy medications during the study are variables that present potential confounding effects for the study results. Therefore, this randomization will be stratified according to the receipt of on-going chemotherapy during enrollment or completion of therapy and according to the use of medication for neuropathy. Patients will be randomized using a computer-generated random allocation sequence through the stratified block randomization method of SAS version 9.1.3 (SAS Institute Inc., Cary, NC, USA) by a statistician ([name]) with no clinical involvement in this trial. Sequentially numbered opaque sealed envelopes containing the randomization assignments will be delivered to the clinical trial center. Allocation concealment will not be broken until the final data analysis report is completed.

### Blinding

In this acupuncture research, it is not feasible to conceal allocation from the practitioners, and the practitioners will be aware of the allocation of each patient. However, treatment and assessment will be performed independently, and the practitioners will not be involved in assessing treatment outcomes. The subjects, the outcome assessors, and the statistician performing the data analyses will be blinded to treatment allocation throughout the study. Patient blinding will be assessed after the end of treatment.

### Intervention

#### Electroacupuncture group

EA will be administered twice weekly for four weeks. Bilateral LI4, TE3, GV39, GV41, SP6, LR3, *Ba Feng*, and *Ba Xie* will be used for acupuncture treatment. The acupuncture points were selected by the consensus of an expert committee composed of professors and researchers who specialize in traditional Korean medicine, on the basis of a literature review [13,14,16-18] and a textbook [20].

Single-use, sterile, filiform acupuncture needles, 0.25 mm in diameter and 40 mm in length (Dongbang Co., Seoul, Korea), will be inserted and stimulated manually, but no specific *de qi* sensation will be provoked because the sensitivity of acupuncture points may vary, especially in patients with chemotherapy-induced peripheral neuropathy. A battery-operated EA device (PG-306 pulse generator, Suzuki Iryoki, Tokyo, Japan) will be connected to the bodies of needles at the acupuncture points. Electrical stimulation will be delivered for 30 minutes at alternating frequencies of 2 and 120 Hz, at an intensity of 80% of each patient’s maximum tolerance.

#### Sham electroacupuncture group

Participants allocated to the sham EA group will receive the sham EA treatment twice weekly for four weeks. The total number of visits and acupuncture needles will be identical to those of the *verum* EA group. The selected sham points are as follows: bilaterally at one point at the middle of the biceps brachii muscle belly and one point at 2 cm vertically below the middle, one point at the middle of the brachioradialis muscle belly and points at 1.5 cm, 3 cm, and 4.5 cm vertically below the middle, four points above the upper part of the patella, one point at the upper third above the medial part of the tibia and points at 1.5 cm, 3 cm, and 4.5 cm vertically below the upper third.

The same type of needles will be shallowly inserted into the sham points with no manipulation for *de qi* and will be connected to a deactivated EA device. No current will be applied but the apparatus will emit the same beeping sound and flashing light continuously for 30 minutes. Sham treatment will be performed by the same doctors who perform the *verum* treatment.

#### Education of practitioners

All EA and sham EA treatments will be performed by doctors of Korean medicine who have been certified by the Korean Ministry of Health and Welfare, have at least three years of clinical experience, and have received more than six years of college education in Korean medicine. Each doctor will take a pre-trial training course for this clinical research. The lead doctor specializing in acupuncture will train all other practitioners and observe their technique periodically to ensure standardization among practitioners. In addition, all study protocols and details, including the recording method for the case report form, outcome assessment methods, and monitoring process, will be standardized between the two centers through workshops.

#### Prohibited concomitant treatments

In both groups, all additional treatments for peripheral neuropathy, including drugs, supplements, and alternative treatments, will be prohibited during the study period.

### Outcome assessment

#### Primary outcome measurement

The primary outcome measure is the European Organization for Research and Treatment of Cancer (EORTC) quality of life questionnaire to assess CIPN (QLQ-CIPN20), a 20-item CIPN-specific questionnaire developed to evaluate patients’ experience of symptoms and functional limitations related to CIPN. The EORTC QLQ-CIPN20 includes three subscales assessing sensory, motor, and autonomic symptoms, with each item measured on a 1 to 4 Likert scale (1, not at all; 4, very much). This questionnaire has been assessed in patients with cancer, who were receiving various chemotherapy regimens, and has been shown to have reliable internal consistency [21].

#### Secondary outcome measurements

CIPN symptom intensity will be assessed using a numerical rating scale (NRS), the clinical tool most commonly used to help patients communicate the intensity of their symptoms. This method has been validated in cancer patients [22,23]. Subjects will be asked to rate their average neuropathic symptoms, including numbness, tingling, and pain, on an 11-point scale (0 = no symptoms; 10 = worst possible symptoms).

The Semmes-Weinstein monofilament (SWM) test will be used to evaluate light touch sensation. The SWM examination is a non-invasive, cost-effective, and objective quantitative sensory test often used in research and clinical practice. A full set of 20 SWM from 1.65- to 6.65-gauge (North Coast Medical, Inc., Morgan Hill, CA, USA) will be used in this trial. This test has been found effective in assessing peripheral neuropathy in cancer patients [24].

The EORTC QLQ-C30 will be used to evaluate health-related QOL (HRQOL) in patients with cancer. The EORTC QLQ-C30 is a 30-item questionnaire assessing five functional scales (physical, role, cognitive, emotional, and social), three symptom scales (fatigue, pain, nausea, and vomiting), and other symptoms and problems frequently encountered in cancer patients (dyspnea, appetite loss, insomnia, constipation, diarrhea, and financial difficulties). Its validity and reliability have been demonstrated [25,26].

NCS is a non-invasive, objective, and reproducible measurement of neurologic function in peripheral neuropathy. Motor conduction will be examined in median and tibial nerves by measuring onset latency, the amplitude of compound muscle action potential and motor conduction velocity. Sensory conduction will be tested in the median and sural nerves by measuring onset latency, the amplitude of sensory nerve action potentials, and sensory conduction velocity. NCS will be performed using the Medelec Synergy system (Oxford Instruments, Abingdon, UK) in an air-conditioned room at constant temperature at Dongguk University Ilsan Oriental Hospital only.

Patient Global Impression of Change (PGIC) is a seven-point categorical scale in which patients rate their overall change in symptoms since the beginning of the study (1 = very much improved, 2 = much improved, 3 = minimally improved, 4 = no change, 5 = minimally worse, 6 = much worse, 7 = very much worse). PGIC has been used in many clinical trials in cancer patients and is recommended to define minimal clinically important differences [8,9,27].

The schedule of procedures and evaluations is presented in Table 1.

**Table 1 T1:** Schedule for treatment and outcome measurement

**Period**	**B**	**T**								**F**	
**Week**		1		2		3		4		8	12
**Informed consent**	x										
**Demographic characteristics**	x										
**EA/Sham EA treatment**		x	x	x	x	x	x	x	x		
**EORTC QLQ-CIPN20**	x				x				x	x	x
**NRS**	x	x	x	x	x	x	x	x	x	x	x
**SWM test**	x				x				x	x	x
**NCS**	x										x
**EORTC QLQ-C30**	x				x				x	x	x
**PGIC**									x	x	x
**Safety assessment**		x	x	x	x	x	x	x	x	x	x

B: baseline, EA: electroacupuncture, F: follow-up phase, NCS: nerve conduction study NRS: numerical rating scale, SWM: Semmes-Weinstein monofilament, PGIC: patient global impression of change. T: treatment phase.

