### Data analysis

The clinical effects of EA on CIPN will be analyzed on an intent-to-treat (ITT) basis. Missing values will be imputed by the last observation carried forward method. The results of the ITT analysis will be compared with those of per-protocol (PP) analysis to evaluate the sensitivity.

Baseline demographic and clinical characteristics of patients will be reported as mean (standard deviation or 95% confidence intervals) or as maximum or minimum for continuous variables, and as frequencies and percentages for categorical variables. Continuous variables will be analyzed by two-sample *t*-tests or Wilcoxon rank sum tests, and categorical variables will be analyzed using the chi-squared or Fisher’s exact test, according to whether or not the data are normally distributed.

Between group differences in primary and secondary outcomes will be analyzed by analysis of covariance, with the baseline score and centers as the covariates and current use of chemotherapy or neuropathy medication as stratified variables, at the second, fourth (primary endpoint), eighth and twelfth weeks. The results for the stratified groups will be compared with the results for the whole subject pool (non-stratified) to determine whether current use of chemotherapy or neuropathy medication is a suitable stratification factor that affects the treatment outcome. Mean differences from baseline to post-treatment in each group will be assessed using paired *t*-tests or Wilcoxon signed rank tests. Repeated measures analysis of variance will be used for assessments at different time points. All statistical analyses will be performed using SAS version 9.1.3 (SAS institute Inc., Cary, NC, USA) by a statistician blinded to patient allocation, and a significance level of 0.05 will be used.

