## Discussion

The increased incidence of cancer has been accompanied by an increase in the number of patients receiving various types of chemotherapy. Although these treatments have enhanced survival rates, they have also increased side effects and treatment-associated symptoms. CIPN is a common and devastating chemotherapy-associated side effect, frequently cited by patients as having a substantial impact on ADLs and QOL [30]. Symptoms of CIPN manifest differently in patients, with diagnoses and assessments primarily dependent on subjective reporting by patients. Therefore, use of appropriate objective outcome measurements, in addition to specific assessments of subjective symptoms, is crucial.

In the present study, to reflect subjectively reported symptoms, we will use the EORTC QLQ-CIPN20 as the primary study outcome to comprehensively assess symptoms of the sensory, motor, and autonomic nervous systems, with the NRS also used as a secondary outcome. In addition to subjective assessments by the patients, the SWM test will be used to evaluate light touch threshold as an objective assessment tool for peripheral neuropathy, quantitatively assessing sensory functions. The NCS is also considered an important objective and quantitative parameter of peripheral nerve function and has been used in many trials of peripheral neuropathy. Acupuncture treatment for CIPN has been reported to improve NCS results [18] as well as peripheral neuropathy of undefined etiology [31] and diabetic neuropathy [32], although these trials were non-randomized, non-blinded, or included patients with peripheral neuropathy caused by other diseases. We have therefore designed an RCT to investigate whether EA has a significant effect on NCS results in patients with CIPN.

This pilot patient-assessor-blinded RCT will investigate the efficacy and safety of EA for CIPN, assess the feasibility and relevance of the intervention and the study design, and provide a clinical foundation for future large-scale, multicenter clinical trials.

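### Applied as written, last observation carried forward would score a nerve that loses its response as zero change in latency and velocity, although planned amplitude can still show the loss

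*Protocol article*

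**What the plan says.** The Secondary outcome measurements section plans three parameters in each of four nerve tests. For motor nerves: "Motor conduction will be examined in median and tibial nerves by measuring onset latency, the amplitude of compound muscle action potential and motor conduction velocity". For sensory nerves: "Sensory conduction will be tested in the median and sural nerves by measuring onset latency, the amplitude of sensory nerve action potentials", followed by sensory conduction velocity. That makes 12 parameters, with no order among them. Testing takes place "in an air-conditioned room at constant temperature at Dongguk University Ilsan Oriental Hospital only", so at one of the two centres.

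Table 1 marks nerve conduction at baseline and at week 12, and nowhere in between.

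The Data analysis section gives one rule for gaps in the data: "Missing values will be imputed by the last observation carried forward method". It names no exception. The model is also common to all outcomes: "Between group differences in primary and secondary outcomes will be analyzed by analysis of covariance, with the baseline score and centers as the covariates".

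The Discussion gives nerve conduction as a reason for the design: "We have therefore designed an RCT to investigate whether EA has a significant effect on NCS results in patients with CIPN".

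**The concern.** Latency and velocity are timings of a recorded potential. Without a potential there is nothing to time, although the patient attended and the test was done. The value is then unobtainable because of the nerve's state, not because of dropout, and better retention would not cure it.

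The situation is plausible here. The Background describes a mostly sensory neuropathy of the toes and fingers, the sural and median sensory nerves are among those tested, and the inclusion criteria admit patients still receiving neurotoxic chemotherapy. A sensory response could therefore be absent at baseline or disappear by week 12.

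If the general imputation rule is applied to such blanks, a complete loss of response enters the latency and velocity analyses as no change. At stake are the group comparison on those parameters and the estimates of their variability, which the Sample size section wants for planning a full-scale trial.

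**Working it through.** The plan gives no figure to reproduce on this point. The check applies its rule to its schedule.

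**Inputs from the article**
- Parameters: latency, amplitude and velocity in median motor, tibial motor, median sensory and sural sensory tests; 4 × 3 = 12 (Secondary outcome measurements).
- Visits: baseline and week 12 (Table 1).
- Imputation: last observation carried forward, no exception; analysis of covariance with the baseline score as covariate (Data analysis).
- Not given: the share of absent responses, or the number of patients tested at the single centre.

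**Step 1. What the rule returns.** With one post-baseline test, the last earlier observation is baseline. Imputed week-12 value = baseline value, so change = baseline − baseline = 0. This holds for latency and velocity of any nerve recordable at baseline and not at week 12, if the blank counts as missing.

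**Step 2. Absent at baseline.** Such a nerve has no earlier value to carry forward and no baseline latency or velocity to serve as covariate. The stated rule and model cannot use it, even if the response returns.

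**Step 3. Reach.** Two sensory tests × 2 parameters = 4 of 12. If motor responses are lost as well, 4 × 2 = 8 of 12. Amplitude is not affected in this way: no response is an amplitude of 0, which is an observed value and needs no imputation.

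**Step 4. The direction can reverse (assumed numbers).** Take 10 nerves per arm, every recordable nerve slowing by 1 m/s, none lost with EA and 4 lost with sham.
- EA mean change: (10 × −1)/10 = −1.0 m/s
- Sham mean change: (6 × −1 + 4 × 0)/10 = −0.6 m/s
- EA minus sham: −0.4 m/s, so the arm that lost more responses looks better.

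A simulation in the same spirit assumed recordable nerves changing by −1 m/s on average (SD 3), with 10% of EA and 30% of sham responses lost. The carried-forward difference was about −0.2 m/s. Rejection rates at the 0.05 level were:

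| Analysis | 10 nerves per arm | 20 nerves per arm |
|---|---|---|
| Velocity, carried forward | 5.0% | 5.5% |
| Velocity, lost response ranked worst | 10% | 19% |
| Amplitude, lost response = 0 | 12% | 23% |

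**Step 5. It can also only dilute (other assumed numbers).** Let velocity = 45 + 4 × ln(amplitude), with log-normal amplitude, a 1 microvolt recording floor, sham nerves losing 40% of amplitude and EA nerves stable. The underlying difference is 4 × ln(1/0.6) = 2.04 m/s.

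| Absent at baseline | Recordable sham responses lost by week 12 | Carried-forward difference | Share of 2.04 |
|---|---|---|---|
| 4% | 11% | 1.79 m/s | 88% |
| 15% | 21% | 1.57 m/s | 77% |
| 32% | 29% | 1.40 m/s | 69% |

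If only half the sham patients worsen, the difference is about 1.0 m/s and the shortfall about 0.13 to 0.34 m/s.

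Both models are illustrations. Their inputs are assumptions, and they disagree on direction.

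**The case against.** The strongest reply is that the article never says an absent response at a completed test counts as a missing value. That the patient attended and was tested is a fair reason not to call it missing, and a coding convention may sit in the full protocol or analysis plan, which is not shown. This makes the point conditional. It does not remove it: the imputation rule is stated universally, a latency that cannot be measured is most naturally left blank, and the article offers no other route for it.

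A reader might infer that the nerve as a whole is scored as unchanged and that the worst deterioration is hidden. The article does not support that. Amplitude is planned in the same nerves and falls to 0, so the loss is visible there provided 0 is entered.

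A reader might also take 8 of 12 parameters as the reach. The rationale is a mostly sensory neuropathy, which supports 4; nothing in the article argues that motor responses will be lost.

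The simulated shrinkage is open to criticism too. Its reference difference averages velocities of nerves that have no response, and its uniform 40% sham loss is invented, although patients who have finished chemotherapy are also eligible. That criticism stands, and no percentage should be quoted as the expected bias.

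Finally, the list of measurements is itself sound, the outcome is secondary and measured at one centre, and this is a 40-patient pilot. All of that stands and limits the weight of the point.

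**Conclusion.** The point holds in a limited, conditional form. If an absent week-12 response leaves latency and velocity blank, the stated rule can only return baseline, and those parameters record zero change for a nerve that lost its response. That conclusion needs only the rule, Table 1 and the fact that a timing requires a response. The reach is mainly 4 of 12 parameters, at most 8.

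Neither the size nor the direction of the resulting bias can be derived from the document. It would be wrong to say that an EA benefit is necessarily pulled toward zero: it may be diluted or reversed, depending on how the recordable nerves behave. Nor is there a stated confirmatory role for latency or velocity that is being compromised.

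Severity is minor. The primary outcome is unaffected, but the Discussion makes nerve conduction a question the trial was designed to answer, so a clarification is worthwhile.

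**What to change.** Amend the missing-value rule in Data analysis; the list of measurements can stay as it is.

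1. State that a non-recordable response at a completed nerve conduction test is not a missing value and is exempt from carrying forward.
2. Enter the amplitude of such a response as 0, at baseline and at week 12.
3. Report by arm the number of nerves that lost or regained a response.
4. For latency and velocity, either summarise them descriptively for nerves recordable at both visits, or analyse them by ranks with a lost response ranked worst.

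Naming amplitude as the lead parameter would be a reasonable preference but is not needed to repair the rule.

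The cost is a few sentences, with no new tests or visits. The small downside is that, under the descriptive option, fewer patients contribute to latency and velocity.
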